### Participant recruitment

A random sample of all participating and non-participating physicians will be drawn and invited for the focus group survey of paediatricians. For the quantitative survey, all paediatricians from the three federal states of Berlin, Brandenburg and Mecklenburg-Western Pomerania will be invited to participate. The difficulty with this target group is in particular a low response rate. On the one hand, this was taken into account by a conservative assumption of the response rate (30%) in the case number calculation. On the other hand, in order to achieve a high acceptance of the target group, a joint address with the BVKJ was made. In addition, each questionnaire contains a personal address in the form of a handwritten note, which demonstrably leads to an increase in the response rate [4]. A reminder is sent to all physicians after 2 weeks and after 4 weeks. In addition, 5 tablets will be raffled as incentives. If no focus groups can be implemented due to insufficient willingness to participate, qualitative telephone interviews will be used as an alternative.

For the focus group survey of the C&A, a random sample of all participants and non-participants is selected and invited from the routine data of the AOK Nordost. For the quantitative survey, a random sample of the participating and non-participating C&A is also selected from the routine data of the AOK Nordost to receive a postal questionnaire. A higher response rate can be expected among C&A than with the target group of physicians. Nevertheless, it is difficult to convince the target group to participate in the surveys. On the one hand, this was taken into account by a conservative assumption of the response rate (40%) in the case number calculation. On the other hand, in order to achieve a high level of acceptance among the target group, a joint approach was made with the BVKJ. In addition, each questionnaire contains a personal address in the form of a handwritten note, with thanks for participating [4]. Proven methods such as incentives and reminders are used to increase response rates and reduce the risk of selection bias through systematic non-participation. In addition, a target group-specific and culture-sensitive approach and linguistic translation of the questionnaire instrument for Turkish, Russian and Arab migration groups will be provided. After 2 weeks and after 4 weeks a reminder will be sent to all C&A. In addition, 30 age-appropriate incentives of max. 30 € each will be raffled off.

### Sample size calculation

#### Qualitative surveys

The number of cases of the qualitative surveys depends on the method of theoretical sampling. The population is not selected according to representativity, but according to the theoretical significance for the research question. Thus, the sample size cannot be determined in advance. The inclusion of further cases is terminated when “theoretical saturation” [21] is reached. For focus groups a sample of 6–8 participants is recommended. Furthermore, following the recommendations 3 focus groups are expected for each target group (*n* = 4 groups with participating and non-participating physicians and insured persons) [22, 23]. This corresponds to a case number of *n* = 72–96 subjects.

#### Quantitative surveys

At the level of paediatricians, all physicians participating in AOK-Junior are included (*n* = 564). With a conservatively expected response rate of 30%, a net sample of *n* = 170 doctors is estimated. Furthermore, a control group of the same size is intended. Approximately 1000 paediatricians will be contacted to reach the sample. The expected course of the study for the target group is shown in Fig. 2.

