**Methods:**

The evaluation is performed on the levels of structural-, process- and results-quality. The cost effectiveness is also assessed by means of a health economic evaluation. In addition to the collection of qualitative and quantitative primary data from participating and non-participating C&A and paediatricians, routine data from a statutory health insurance are used in the evaluation. Furthermore, a cross-sectional design is used to evaluate the structure and process quality. The effectiveness is evaluated in longitudinal section design on the basis of the secondary data. The quantitative surveys include net *n* = 1096 C&A and *n* = 340 pediatricians. For the focus groups, a sample of 72 to 96 parents as well as pediatricians will be sought by using the method of theoretical sampling.

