### Study population

The underlying study population consists primarily of an IG and a CG at paediatricians as well as C&A level. The AOK-Junior selective contract is implemented in entire catchment area of the AOK Nordost. At the level of paediatricians, all participating physicians are included in the quantitative survey. The CG includes doctors who are also organised in the BVKJ but do not participate in the selective contract AOK-Junior. For the inclusion of the CG, it is considered that these are active in catchment areas that are as comparable as possible. A sub-sample will be taken for the qualitative surveys. Thereby, an adequate representation of the range of catchment areas of established paediatricians is taken into consideration.

At the level of the insured, the study population is drawn on the basis of routine data. The participants of the IG are C&A from birth up to and including the age of 17. Thus for each module its own population is needed. The exception is the target agreement on overweight. In the CG are C&A who are also insured with the AOK, but who do not participate in the AOK-Junior prevention programme. In order to ensure comparability between participating and non-participating insured persons, a CG is formed for the IG on the basis of routine data using the characteristics of sex, age and comparable region by means of PS matching.

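### About 1000 paediatricians contacted at the stated 30% response do not give the stated net sample of 340 in two groups of equal size

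*Protocol article*

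**What the plan says.** Under Sample size calculation, Quantitative surveys, the protocol article plans the paediatrician survey in four steps:

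- Participating doctors are all surveyed: "all physicians participating in AOK-Junior are included (*n* = 564").
- Their expected return is "With a conservatively expected response rate of 30%, a net sample of *n* = 170 doctors is estimated".
- For the comparison, "Furthermore, a control group of the same size is intended".
- The effort needed is given as "Approximately 1000 paediatricians will be contacted to reach the sample".

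The Methods paragraph of the Abstract gives the resulting net total as "340 pediatricians", that is, twice 170. Participant recruitment repeats the response assumption for paediatricians ("this was taken into account by a conservative assumption of the response rate (30%) in the case number calculation") and gives no different rate for non-participants.

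The source of the controls is described in two ways. Study population says "The CG includes doctors who are also organised in the BVKJ but do not participate in the selective contract AOK-Junior". Participant recruitment says of the quantitative survey that "all paediatricians from the three federal states of Berlin, Brandenburg and Mecklenburg-Western Pomerania will be invited to participate".

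**The concern.** The number contacted, the response rate and the net sample are tied by one multiplication, so any two of them fix the third. Here the three printed values do not satisfy it. The participating group's figure does follow from its inputs, so on the natural reading the whole mismatch lies with the controls.

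This survey supplies the comparison of structural features between participating and non-participating physicians (Evaluation of the structural quality) and the questionnaire check of the focus-group results (Process evaluation). A reader of the Abstract will expect about 340 doctors in two balanced groups. If the plan's own inputs deliver something smaller and unbalanced, the stated sample is wrong before the survey starts, and a later shortfall could be mistaken for poor recruitment.

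**Working it through.** **Inputs**, all from the protocol article:

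- Participating paediatricians, all contacted: 564 (Quantitative surveys)
- Response rate: 30% (Quantitative surveys; Participant recruitment)
- Net participating group: 170, with controls of the same size (Quantitative surveys)
- Net total: 340 (Abstract, Methods)
- Contacted: approximately 1000 (Quantitative surveys)

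**Formulas.** Net = contacted × response rate. Contacts needed = net ÷ response rate.

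**1. Reproduce the participating group.** 564 × 0.30 = 169.2. This agrees with 170.

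**2. Reproduce the total, taking 1000 to include the 564.** 1000 × 0.30 = 300, not 340. The gap is 40 returns, and 40 ÷ 340 = 12%.

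**3. Split the 300.** Controls contacted: 1000 − 564 = 436. Control returns: 436 × 0.30 = 130.8, about 131 instead of 170. The gap is 39 returns, and 39 ÷ 170 = 23%.

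**4. What would deliver 340.**

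- Contacts for the total: 340 ÷ 0.30 = 1,133.
- Contacts by group: 170 ÷ 0.30 = 567 controls, and 564 + 567 = 1,131. Either way, about 1,130.
- Response needed if contacts stay at 1000: 340 ÷ 1000 = 34% overall, or 170 ÷ 436 = 39% among controls with participants held at 30%.

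**5. How much can "approximately" absorb?**

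| Contacted | Returns at 30% | Control returns |
|---|---|---|
| 950 | 285 | 116 |
| 1000 | 300 | 131 |
| 1050 | 315 | 146 |
| 1100 | 330 | 161 |
| 1133 | 340 | 171 |

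The stated sizes are reached only near 1,130 contacts.

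**6. The other reading: 1000 means controls only.** 1000 × 0.30 = 300 controls, not 170. The total would be 169 + 300 = 469, not 340. A control return of 170 would then imply 170 ÷ 1000 = 17% response, which the article does not state.

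**7. Comparison within the same section.** The survey of children and adolescents uses the same formula and does reproduce: 1096 ÷ 0.40 = 2740, as printed. The mismatch is confined to the paediatrician survey.

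**The case against.** The best defence is that these are planning projections, hedged in the text, and that 30% is called conservative. The plan adds a joint approach with the professional association, handwritten notes, two reminders and a raffle, and needs only 34% overall to reach 340 from 1000 contacts. That is a modest departure. It stands as a reason not to expect a large practical loss. It does not make the printed figures agree, because the article applies 30% itself to obtain 170.

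It can also be said that the 1000 is ambiguous. The sentence follows directly on the one about the control group and does not say whether the 564 are counted. This stands: the 169/131 split and the location of the shortfall depend on the 1000 including the participants. Under the controls-only reading there would be more controls than stated, not fewer. But neither reading gives 170 and 340.

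Fig. 2, the flowchart for this survey, is not available here and may give contacts by group. It could settle what the 1000 means, but it cannot reconcile the printed text of the Abstract and the sample-size section.

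Two stronger readings are tempting:

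- A reader might infer that the survey loses planned power. The article sets no significance level, power or effect size for paediatricians; the 5% level and 80% power in that section belong to the survey of children and adolescents. Borrowing a two-sided 5% level and 80% power purely as an assumption, the detectable standardised difference is (1.960 + 0.842) × √(1/n₁ + 1/n₂). This gives 0.30 for 170/170 and 0.33 for 169/131, a small change.
- A reader might infer that limiting controls to members of the professional association makes the shortfall larger. No count of member or non-member paediatricians is given, so the effect cannot be computed. One passage may also describe who belongs to the control group and the other who is invited.

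**Conclusion.** The point holds. At the single stated response rate, about 1000 contacts do not yield a net 340 with two groups of 170.

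Assuming that the 1000 includes the 564 participants and that 30% applies to both groups, the expected net is about 300, split about 169 to 131. The control group is about 23% below its stated size and the gap is about 130 contacts, more than "approximately" can reasonably cover.

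The consequence is a misstated net sample and an unbalanced comparison. It is not a failed power calculation, and it does not touch the main question on early detection, which is assessed from routine data. The difference between the two descriptions of the control frame is a separate inconsistency of unknown effect on these numbers.

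**What to change.** 1. In the sample-size section, say whether the approximately 1000 includes the 564 participating doctors.
2. If it does, restate the expected net sample there and in the Abstract as about 300 (169 participating, 131 control), and drop the equal-size statement.
3. Two alternatives would keep 340. One is to state about 1,130 contacts, about 567 of them controls, if that many eligible non-participants exist. This may not be possible: all paediatricians in the three states are already to be invited, so about 1000 may be the whole frame, and the article gives no count. The other is to state and justify a separate control response rate, which would have to be about 39% with 436 controls.
4. Reconcile the control frame in Study population (members of the professional association) with the invitation in Participant recruitment (all paediatricians in the three states), and base the contact number on the reconciled frame.

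Restating the net sample is a correction of text only; its cost is a smaller stated sample. The 1,130-contact option adds about 130 mailings.

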**Fig. 2 Fig2:**
[figure not shown]
Flowchart for the primary survey among the target group of paediatricians based on the STROBE Statement

At the level of the C&A, all patients who have used the services are included in the IG as part of the secondary data analyses. Using PS matching, a suitable CG is drawn from the secondary data in a ratio of 1:1. The collection of primary data takes place in a sub-sample, whose case number was calculated on the basis of the primary outcome parameter of the health-related quality of life. A 2 × 3-factorial design is used to compare the intervention with standard care (IG/CG) (factor 1), taking into account multiple factors, e.g. the region (factor 2). To demonstrate expected small effects at the significance level of α ≤ 0.05 and a power of 80%, a net sample of *n* = 1096 (*n* = 548 per group) is required for analysis. With a conservatively expected response rate of 40%, a sample of *n* = 2740 is invited to participate. The case number planning and the analysis methods are selected in order to adjust for covariates (e.g. gender). The expected course of the study for the target group is shown in Fig. 3.

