### Objectives of the study

The main question is intended to answer the question to what extent the AOK-Junior programme can detect diseases in C&A earlier. The global hypothesis tests whether the intervention (participation in the selective contract AOK-Junior) improves the effectiveness of early disease detection compared to standard care. Furthermore, it is assumed that the selective contract is superior in further effectiveness parameters (response, satisfaction) as well as in cost-effectiveness (costs, cost-effectiveness ratio).

The questions for the individual levels of the evaluation project are as follows:
Structural quality: Which structures are used to implement AOK-Junior?Process quality: Which promoting and hindering factors can be identified for the implementation of the selective contract?Outcome quality: What effects does AOK-Junior have on the participants?Health economic evaluation: How high are the programme costs of AOK-Junior? What is the cost-effectiveness of the selective contract and individual service modules?Question for further development: Which recommendations for action can be derived for the further development of selective contractual care?

Furthermore the following hypotheses will be examined:
H_1_: Diseases are discovered earlier in the intervention group (IG) than in the control group (CG).H_2_: More diseases are discovered in IG than in CG.H_3_: Early detection of disease in IG leads to earlier therapy than in CG.H_4_: In the IG, follow-up costs compared to the CG are avoided.H_5_: Early detection of disease is more cost-effective in the IG (cost per discovered case) than in the CG.

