#### Quantitative analyses

The data evaluations are initially performed descriptively. The hypotheses developed are also tested for inferential statistics. In order to ensure comparability between participating and non-participating insured persons, a CG is formed for the IG on the basis of the routine data using the characteristics gender, age and comparable region. Participants from both groups are brought together with PS matching at the individual level. The analyses of the primary data take into account in particular covariates for which it was not possible to match at the secondary data level, such as socio-economic status and migration background. The influence of the selective contract is checked using ANCOVA. The analyses are carried out with the software programs SAS, SPSS and Microsoft Excel.

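### The routine-data intervention group is defined by service use in one place and by participation elsewhere; under the use rule, enrolled non-users fall in neither group and detection tends to be inflated by an unknown amount

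*Protocol article*

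**What the plan says.** The protocol article describes the routine-data groups in four places.

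- **Objectives of the study.** The global hypothesis tests "whether the intervention (participation in the selective contract AOK-Junior) improves the effectiveness of early disease detection compared to standard care". The exposure is participation.
- **Study population.** On the intervention side: "The participants of the IG are C&A from birth up to and including the age of 17". This gives an age range and no condition of use. It is followed by: "Thus for each module its own population is needed". On the control side: "In the CG are C&A who are also insured with the AOK, but who do not participate in the AOK-Junior prevention programme". Controls are selected "using the characteristics of sex, age and comparable region by means of PS matching".
- **Sample size calculation, quantitative surveys (text after Fig. 2).** Here the rule is that "all patients who have used the services are included in the IG as part of the secondary data analyses", with a control group (CG) matched 1:1.
- **Statistical analysis, quantitative analyses.** The comparison is again by participation: "In order to ensure comparability between participating and non-participating insured persons, a CG is formed for the IG on the basis of the routine data".

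The outcomes of this comparison are time of detection (H1) and incidence rate (H2) of chronic disease. Cost per discovered case (H5) builds on the same detections. The services include the U10, U11 and J2 examinations and the eye, lung and skin checks. They also include a module for participants who have allergic rhinitis and a target agreement for participants who are overweight or obese. The study population section names the overweight agreement as an exception to the module-specific populations but does not say how it is handled.

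**The concern.** Participation and use are different exposures. Participation is fixed at enrolment. Use happens later, and in this programme it is usually a diagnostic contact or follows from a diagnosis. If use decides who enters the IG, membership is partly determined by the process that generates the outcome. Nothing on the control side corresponds to that. Children with frequent diagnostic contact also exist among the controls, but there they are mixed with children who have little.

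Two things are at stake. The estimate would not answer the stated question, which is about participation. And the IG could show more detected disease than the CG when the contract has changed nothing. The study is meant to inform the further development of the contract and the possible extension of its services to standard care, so an artefact of group definition could be read as support for H2. Detected cases are also the denominator of cost per case, so H5 would be distorted too.

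**Working it through.** **Step 1: apply the stated rules to each kind of child.**

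| Child | IG by use rule | IG by participation | CG |
|---|---|---|---|
| Enrolled, used a service | yes | yes | no |
| Enrolled, used none | no | yes | no |
| Not enrolled | no | no | eligible for matching |

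The two IG definitions differ in the second row. Under the use rule that child belongs nowhere, and no section assigns such children to a group.

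**Step 2: can matching repair it?** The matching variables are sex, age and region. None measures diagnostic contact, earlier morbidity or opportunity for detection. Socio-economic status and migration background are to be adjusted for in the primary survey data, not in this comparison.

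**Step 3: is there a planning figure to reproduce?** Not for this comparison. The only sample size for children and adolescents is for the quality-of-life survey: 1096 net, and 1096 / 0.40 = 2740 invited. The second figure reproduces exactly but has no bearing here.

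**Step 4: how large could the distortion be?** Let u be the share of enrolled children who use a service, and r the ratio of detection in users to detection in enrolled non-users. The article gives neither. Both ranges are assumptions: u from 30% to 90%, r from 1.5 to 3.

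Suppose participation has no effect, so that detection among all enrolled children equals detection d in controls:

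- u × (users) + (1 − u) × (non-users) = d, with users = r × non-users
- non-users = d / (u·r + 1 − u)
- apparent ratio, users versus CG = r / (u·r + 1 − u)

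Example: u = 0.5, r = 2 gives 2 / (1.0 + 0.5) = 1.33.

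| u | r = 1.5 | r = 2 | r = 3 |
|---|---|---|---|
| 30% | 1.30 | 1.54 | 1.88 |
| 50% | 1.20 | 1.33 | 1.50 |
| 70% | 1.11 | 1.18 | 1.25 |
| 90% | 1.03 | 1.05 | 1.07 |

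With an IG of all enrolled children the ratio is 1.00 in every cell, by construction. At r = 1 the use rule also gives 1.00.

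**Step 5: how many children are left out?** Of about 65,000 enrolled (Intervention section), 65,000 × (1 − u) fall in neither group: 45,500 at u = 30% and 6,500 at u = 90%.

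**Step 6: timing (H1).** The formula concerns the rate of detection and says nothing about when it occurs. An additional examination can bring a diagnosis forward. But using an age-windowed module requires the child to have reached that window, which can push the recorded date later. The net direction is not determined.

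**The case against.** The strongest reply is that the sentence on service use is loosely worded rather than a settled rule. It stands in the sample size section, where it contrasts taking everyone from the routine data with surveying a sub-sample, and it does not say that only users enter. The study population and statistical analysis sections describe participants against non-participants. This stands in part. A reader might infer that the study has definitely adopted a use-defined IG, and the article does not support that. It supports a conflict between definitions. The use sentence is nevertheless the one that says who enters the IG of the routine-data analysis, and no other section overrides it.

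A second reply is that effects among module users are a legitimate question, since separate populations per module are foreseen and the service modules are to be evaluated individually. That is fair, but it is a different question from the global hypothesis, and it would need controls with comparable eligibility and time origin.

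A third reply is that the size is speculative. It is. A reader might be tempted to insert the J1 uptake quoted in the background (46–48%); at u = 0.48 and r = 2 the formula gives 2 / (0.96 + 0.52) = 1.35. The article does not support that as an estimate. J1 is a standard-care examination in the general population, not use of AOK-Junior services among enrolled families, and the value of r has no source. At 90% uptake the same r gives 1.05.

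Finally, controls are not simply all non-participants. They are AOK-insured and matched 1:1, so age and insurance are at least partly handled. Diagnostic contact is not.

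**Conclusion.** The concern holds as a conflict of definitions with a foreseeable consequence. The article defines the routine-data IG by service use in one section and by participation in three others, and the use rule leaves enrolled non-users without a group. If the use rule is applied, detection in the IG tends to be inflated for H2, and cost per case in H5 is affected, even with no effect of participation.

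The size cannot be derived from the document. Under the assumed uptake of 30–90% and detection ratio of 1.5–3, a null effect appears as about 1.03 to 1.88. It is small if nearly all enrolled children use a service and vanishes if users and enrolled non-users have equal detection; the latter is unlikely where the service is itself a detection examination or presupposes a diagnosis.

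A reader might also infer that H1 is biased towards earlier detection. The document does not establish that; the effect on timing could go either way.

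**What to change.** In the sample size section, replace the use-based sentence. Define the IG for the main routine-data comparison as all enrolled children who are age-eligible for the module, whether or not they used it. Compare them with matched non-participants from the same index date or age. Align the study population and statistical analysis sections with this one definition. Report the service-user comparison as a labelled supplementary, module-level analysis.

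The cost is wording and a renewed extraction from routine data already held. There are two drawbacks. The main estimate is diluted by enrolled non-users: if a service raised detection in users by a ratio of 1.3 and there were no selection, the participation ratio would be 1 + 0.3u, that is 1.09 at 30% uptake and 1.27 at 90%. And families still choose whether to enrol, so self-selection into the programme remains and this change does not address it.
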